
In this randomized sham-controlled trial, functional Magnetic Resonance Imaging (fMRI) and Motor Evoked Potentials (MEP) were integrated in addition to the standardized upper limb motor function scale. The main objectives of this experiment are as follows: 1. To analyze the dynamic changes in brain network structure and functional connectivity after intervention. 2. To establish a correlation model between clinical functional improvement and neuroimaging/electrophysiological indicators. 3. Explain the neural remodeling mechanism of upper limb functional rehabilitation after stroke (23). Core scientific hypothesis: High-frequency rTMS targeting the contralateral dorsal Premotor Cortex (cPMd) can significantly promote the recovery of upper limb motor function in patients with severe stroke. This study will provide new evidence for the mechanism of rTMS regulating neural compensation after stroke, and promote the development of precise neurorehabilitation strategies.

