### Participants and eligibility

#### Enrollment criteria

The following are the inclusion criteria: (1) meet the diagnostic criteria for stroke: according to the “Guidelines for the Diagnosis and Treatment of Cerebral Hemorrhage in China (2019)” or “Guidelines for the Diagnosis and Treatment of Acute Ischemic Stroke in China (2018),” the diagnosis is confirmed by head CT/MRI imaging; (2)characteristics of stroke attack: initial unilateral onset, or no sequelae of neurological deficit left by previous stroke attacks; (3) vital signs and consciousness state: Vital signs are stable for ≥ 24 h, Glasgow Coma Scale (GCS) score = 15 points;(4) age range: 18–75 years old; (5) upper limb motor deficit: baseline Fugl-Meyer Upper Limb Motor Function Rating Scale (FMA-UE) score ≤ 26 points (suggesting severe motor impairment) (18); (6) informed consent: Voluntary written informed consent; (7) Recruiting patients within 1 week to 6 months after stroke.

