#### fMRI scan

The acquisition will be carried out by the same professional and technical personnel in the magnetic resonance room of our hospital according to the prescribed acquisition sequence and parameters. Before the start of data collection, the contraindications of MRI examination will be checked again to see that the subjects do not have metal stents, pacemakers, etc., and the scanning steps will be introduced in detail, and the subjects will be instructed to lie flat on the scanning table in a resting and quiet state, and at the same time wear noise-canceling headphones to minimize the impact of the noise of the examination equipment on the collection results. During the scan, the subject will be asked to close his eyes and relax as much as possible, keep his head and body still, do not think or sleep, and start the scan after the subject is used to it. T1 structural image: the magnetization intensity will be used to prepare the gradient echo sequence, and the scanning parameters are as follows: time of repetition (TR) = 1900 ms, time of echo (TE) = 2.52 ms, field of view (FOV) = 250 mm × 250 mm, flipangle (FA) = 9°, matrix (Matrix) = 256 × 256, Thickness = 1.0 mm, Gap = 0 mm, voxel size = 1 × 1 × 1 mm^3^. rs-fMRI scanning: a gradient echo single excitation echo plane imaging is used, and the scanning parameters are: repetition time = 2000 ms, echo time = 13 ms, field of view = 192 mm × 192 mm, inversion angle = 90°, matrix = 64 × 64, layer thickness = 3.0 mm, layer spacing = 1 mm, voxel size = 3 × 3 × 3 mm^3^.

Data processing will be pre-processed with functional imaging data using resting-state functional magnetic resonance imaging software. Lesion size and fraction of anisotropy (FA) within the posterior internal capsule (PLIC) are determined by diffusion tensor imaging (DTI) to assess the integrity of the corpus callosum (CST). Anisotropy fraction (FA) values and mean anisotropy fraction asymmetry index (FAAI) are key indicators to assess bundle integrity (33, 34). DTI datasets will be processed using the Pipeline for Analyzing Brain Diffusion Images (PANDA) toolkit^1^ to obtain the average FA and FAAI values of patients from the whole group (35). The PANDA toolkit mainly includes the following steps: data preprocessing, diffusion tensor model fitting and index calculation, fiber tracing, brain structural network construction, and result output. Bilateral PLIC, Pontine and Anterior Gyrus will be selected as the target regions.

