#### Data processing and analysis

We will use the Shapiro–Wilk test to assess whether the data are normally distributed. For data that conform to the normal distribution, it will be presented as means and standard deviations; for non-normally distributed data, it is presented as a median and interquartile range. For continuous data, one-way ANOVA will be used for between-group mean comparison; for categorical data, the chi-square test will be used for data analysis. The FMA-UE scale, BI score, NIHSS scale and imaging indicators [anisotropy score (FA) value and mean anisotropy score asymmetry index (FAAI)] will be analyzed by repeated measures ANOVA and multivariate ANOVA, respectively, in which the inter-group factors are high-frequency group, low-frequency group and sham stimulation group, and the intra-group factors are time (T0-T3), and multiple comparisons of LSD correction will be performed. The correlation between clinical scale data and imaging index data will be tested by Spearman or Pearson correlation tests. The level of statistical significance will be set at *p* < 0.05. In order to compare the therapeutic effects of different repetitive transcranial magnetic regimens, a two-factor mixed design analysis of variance including the inter-group factor “group” and the intra-group factor “time” will be used for clinical manifestations and electrophysiological changes. The DTI dataset will be processed via the PANDA toolkit to obtain the average FA and FAAI values for the entire population of patients.

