## Discussion and conclusions

In recent years, many studies have confirmed that repetitive transcranial magnetism (rTMS) can effectively improve the motor function of stroke hemiplegic patients (36, 37). But there are also studies that have found negative results, and some patients even have functional degeneration (38, 39). These evidences suggest that standardized rTMS protocols based on the theory of bilateral primary motor cortex (M1) IHI imbalance have limitations in clinical practice (40). Patients with chronic stroke accompanied by severe motor impairments have widespread damage to the neural pathways in the affected hemisphere, resulting in the M1 region being unable to effectively promote motor function recovery, ultimately leading to the failure of repetitive transcranial magnetic stimulation (rTMS) therapy (41). Therefore, this study will focus on cPMd therapies based on the latest “bimodal equilibrium-recovery model” (12).

This study is the first to systematically evaluate the efficacy of high-frequency rTMS targeting the anterior dorsal motor cortex (cPMd) on the unaffected side on severe upper limb motor dysfunction after stroke. Based on the theoretical framework of the Bimodal Balance-Recovery Model (BBRM), we propose the following core mechanism hypothesis: when the corticospinal tract on the affected side is severely damaged, high-frequency stimulation of the unaffected side cPMd can significantly improve the recovery of motor function by enhancing transhemispheric compensatory nerve remodeling. This effect may involve: (1) reversal of inhibitory regulatory imbalance: regulation of pathological interhemispheric inhibition; (2) activation of compensatory pathways: promote synaptic plasticity of the unaffected hemisphere-spinal anterior horn network. The results of this study will provide key evidence for precision neurological rehabilitation: in the future, rTMS treatment plans need to stratify patients according to the time window of injury, lesion localization and CST integrity, so as to achieve individualized intervention. In addition, the cPMd high-frequency stimulation paradigm is expected to be extended to the neuromodulation of multi-domain dysfunctions such as aphasia and swallowing disorders after stroke.

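### The correlation that is to link clinical recovery with imaging has no term for arm, so with post-treatment or change values it can reflect the group effect alone

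*Protocol article*

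**What the plan says.** The Introduction lists three main objectives. The second is "To establish a correlation model between clinical functional improvement and neuroimaging/electrophysiological indicators", and the third is to explain the mechanism of neural remodelling.

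Under Data processing and analysis, the only method that relates the two kinds of data is this: "The correlation between clinical scale data and imaging index data will be tested by Spearman or Pearson correlation tests". The text does not state which time points are used, whether values are raw or changes from baseline, or whether the arms are pooled.

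The other models in that section do not fill the gap. The clinical scales and the imaging indices "will be analyzed by repeated measures ANOVA and multivariate ANOVA, respectively, in which the inter-group factors are high-frequency group, low-frequency group and sham stimulation group", with time as the within-patient factor. FA and FAAI appear there as outcomes and nowhere as predictors or covariates of a clinical result.

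The Abstract classes the fMRI and MEP measures as exploratory and says that assessments are made before and after the intervention.

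**The concern.** A simple correlation across a three-arm trial mixes two sources of association: how patients vary together within an arm, and how the arm means vary together. Only the first bears on whether patients whose imaging changes more also recover more. The second is another way of showing that treatment moved both measures.

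The plan expects FMA-UE to differ strongly by arm and also compares FA and FAAI between arms over time. If both expectations are met, the across-arm coefficient will be non-zero even when imaging and recovery are unrelated within every arm. A significant result could then be reported under the second and third objectives as evidence of mechanism when it only restates the group comparison.

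**Working it through.** **Inputs from the protocol article, Sample size calculations.** FMA-UE means 11.4, 4.7 and 2.8 (high frequency, low frequency, sham); standard deviations 1.4, 0.9 and 1.3; 9 evaluable and 12 enrolled per arm. The 5% significance level is in Data processing and analysis. The plan gives no figure for the correlation, so there is none to reproduce.

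**Assumptions.** (a) The within-arm correlation is zero. (b) The imaging index shifts between arms in the same pattern as the FMA-UE means, with effect size f (SD of the arm means divided by the within-arm SD) of 0, 0.1, 0.25 or 0.5. (c) The FMA-UE SD is as planned or, alternatively, 5. The value 5 is used because the F-test named in the sample size section needs 9 per arm only at an SD of about 4.75 to 5.0. That mismatch is a separate matter and nothing here rests on it.

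**Step 1, share of FMA-UE variance that lies between arms.** The grand mean is (11.4 + 4.7 + 2.8)/3 = 6.3. The between-arm variance is (5.1² + 1.6² + 3.5²)/3 = (26.01 + 2.56 + 12.25)/3 = 13.61. The mean within-arm variance with the planned SDs is (1.96 + 0.81 + 1.69)/3 = 1.487.
- Planned SDs: η² = 13.61/(13.61 + 1.487) = 0.902.
- SD 5: η² = 13.61/(13.61 + 25) = 0.352.

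**Step 2, the same share for the imaging index.** η² = f²/(1 + f²), which gives 0.0099, 0.0588 and 0.200 for f = 0.1, 0.25 and 0.5. The distance between the high-frequency and sham means is 8.6/√13.61 = 2.33 SDs of the arm means. These values of f are therefore imaging shifts of 0.23, 0.58 and 1.17 within-arm SDs.

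**Step 3, correlation produced by the arm means alone.** r = √(η² for FMA-UE × η² for imaging).
- Planned SDs: √(0.902 × 0.0099) = 0.09; √(0.902 × 0.0588) = 0.23; √(0.902 × 0.200) = 0.42.
- SD 5: √(0.352 × 0.0099) = 0.06; √(0.352 × 0.0588) = 0.14; √(0.352 × 0.200) = 0.27.

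The two-sided 5% critical value at n = 36 is 0.329.

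**Step 4, how often the test is falsely significant.** Simulated trials with 12 per arm, zero within-arm correlation, Pearson test:

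| Imaging shift f | Planned SDs | SD 5 | Arm-adjusted |
|---|---|---|---|
| 0 | about 5% | about 5% | about 5% |
| 0.1 | 9% | 6% | about 5% |
| 0.25 | 28% | 14% | about 5% |
| 0.5 | 78% | 36% | about 5% |

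With 9 per arm (n = 27) and f = 0.5, the simple test is falsely significant in 65% of trials (planned SDs) or about 29% (SD 5). Spearman behaves similarly: with a high-frequency minus sham imaging shift of 1.0 within-arm SD, planned SDs and n = 36, Pearson is significant in 66% of trials and Spearman in 57%.

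**Step 5, baseline values.** Randomisation precedes treatment, so baseline FA or FAAI cannot be shifted by arm except by chance. That is the f = 0 row, and the simple test holds its level there.

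**The case against.** The strongest reply is that the article is silent rather than wrong. It does not say that the arms are pooled or which values are correlated, and an article may leave such detail to a full protocol or analysis plan. The phrase "to obtain the average FA and FAAI values for the entire population of patients" describes the processing of the diffusion data, not the correlation, so a reader who infers a commitment to pooling from it goes too far. This stands, and it is why the point is conditional. What remains is that the method named has no place for arm. Separate within-arm correlations would avoid the artefact, but none is stated, and with 9 to 12 patients per arm they would need |r| of about 0.67 to 0.58 to reach significance.

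Second, the artefact needs an imaging index that itself moves by arm. The article says that FA and FAAI "are key indicators to assess bundle integrity", and if they serve only as baseline measures of tract integrity, treatment cannot create the association. This also stands. Against it, the second objective concerns improvement, and the plan analyses FA and FAAI over time, so change values are a natural reading.

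Third, the documents support no particular imaging shift, and f = 0.5 is more than one within-arm SD after three weeks of treatment. A reader might take 78% as the expected error rate. It is one assumed case at the top of the range shown.

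Fourth, a reader might infer that the plan leaves untested a hypothesis that benefit depends on corticospinal damage. The Discussion says that "when the corticospinal tract on the affected side is severely damaged, high-frequency stimulation of the unaffected side cPMd can significantly improve the recovery", and entry rests on an FMA-UE "score ≤ 26 points (suggesting severe motor impairment") rather than on tract damage. But that sentence describes a population and does not claim that the effect differs by degree of damage. The Introduction words the core hypothesis for severe stroke, which the group comparison does address. The statement that "rTMS treatment plans need to stratify patients according to the time window of injury, lesion localization and CST integrity" is placed in the future. The documents do not support the stronger reading.

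**Conclusion.** The point holds in a limited form. Followed literally across the three arms with post-treatment or change values, the named correlation can present the group effect as an association between recovery and imaging.

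Its size depends on an unstated imaging shift. At n = 36 the false-significance rate runs from about 5% (no shift) to 78% (f = 0.5) with the planned SDs, and from about 5% to 36% with an SD of 5. It further assumes zero within-arm correlation and an imaging shift in the same pattern as the FMA-UE means. Correlations with baseline imaging are not affected.

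Only the mechanistic, exploratory part of the trial is touched. The primary FMA-UE comparison is not. The change is worth making because it is nearly free and holds the error rate at about 5% in every case examined.

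**What to change.** In Data processing and analysis, replace the simple correlation with a partial correlation adjusted for arm (Pearson or rank) between change in FMA-UE and change in the imaging index, and state the time points. Analyse baseline FA and FAAI separately, as prognostic measures. Label these results exploratory and make no claim of mechanism from an unadjusted correlation. The adjusted coefficient is still an association between two measures taken after randomisation, so it does not establish mechanism by itself.

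The cost is a few lines of text, no new data and two degrees of freedom. With r = t/√(df + t²), the critical value at n = 36 moves from 2.032/√(34 + 2.032²) = 0.329 to 2.037/√(32 + 2.037²) = 0.339.

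A test of arm by baseline FAAI is optional. It would be imprecise: even if a slope of 1 SD per SD existed in the high-frequency arm only, its power would be about 43% at n = 27 and 60% at n = 36.

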## Discussion and conclusions

In recent years, many studies have confirmed that repetitive transcranial magnetism (rTMS) can effectively improve the motor function of stroke hemiplegic patients (36, 37). But there are also studies that have found negative results, and some patients even have functional degeneration (38, 39). These evidences suggest that standardized rTMS protocols based on the theory of bilateral primary motor cortex (M1) IHI imbalance have limitations in clinical practice (40). Patients with chronic stroke accompanied by severe motor impairments have widespread damage to the neural pathways in the affected hemisphere, resulting in the M1 region being unable to effectively promote motor function recovery, ultimately leading to the failure of repetitive transcranial magnetic stimulation (rTMS) therapy (41). Therefore, this study will focus on cPMd therapies based on the latest “bimodal equilibrium-recovery model” (12).

This study is the first to systematically evaluate the efficacy of high-frequency rTMS targeting the anterior dorsal motor cortex (cPMd) on the unaffected side on severe upper limb motor dysfunction after stroke. Based on the theoretical framework of the Bimodal Balance-Recovery Model (BBRM), we propose the following core mechanism hypothesis: when the corticospinal tract on the affected side is severely damaged, high-frequency stimulation of the unaffected side cPMd can significantly improve the recovery of motor function by enhancing transhemispheric compensatory nerve remodeling. This effect may involve: (1) reversal of inhibitory regulatory imbalance: regulation of pathological interhemispheric inhibition; (2) activation of compensatory pathways: promote synaptic plasticity of the unaffected hemisphere-spinal anterior horn network. The results of this study will provide key evidence for precision neurological rehabilitation: in the future, rTMS treatment plans need to stratify patients according to the time window of injury, lesion localization and CST integrity, so as to achieve individualized intervention. In addition, the cPMd high-frequency stimulation paradigm is expected to be extended to the neuromodulation of multi-domain dysfunctions such as aphasia and swallowing disorders after stroke.

The protocol has some limitations. First, the small sample size and single-center study design may affect the universality of the results. Second, due to clinical feasibility considerations, the timing of conventional treatment and repeated transcranial magnetic therapy is not strictly regulated, which may affect the interpretation of efficacy-although the randomization design may partially alleviate the time difference between groups. Future studies should control this variable more strictly. Third, this study will only evaluate the resting motion threshold of the contralateral hemisphere of the lesion before the intervention, and does not evaluate the bilateral hemispheres synchronously before and after the intervention, which will limit the verification of the theory of physiological effects of transcranial magnetic therapy and hemispheric imbalance. In addition, some subjects did not record the coordinate data of the hot zone of hand movement, which will lead to limitations in the comparison of differences between superior neural targets and hot zone targets.
